#### Experimental Group Receiving AR-Guided CPAP Therapy: Proposed System

Figure 1 illustrates the proposed system architecture, consisting of a camera module, an Edge-AI computing module, and a display module. The camera module captures the user’s facial and hand images, while the Edge-AI computing module processes these images to detect relevant features and perform calculations to ensure a proper nasal mask fit and verify the accuracy of the wearing procedure. The display module presents the measurement results and offers real-time feedback on the recommended nasal mask size, following the mask sizing guidelines provided by ResMed [18].

**Figure 1 figure1:**
[figure not shown]
Proposed system architecture.

#### Standard Care Group

Participants assigned to the standard care group will have their mask size visually checked by a case manager, who will also teach them how to use the CPAP machine.

### Primary Outcomes

#### Objective Measure: Adherence to CPAP Therapy

CPAP adherence will be monitored daily using AirView, a cloud-based remote monitoring system. The research team will explain the study objectives to participants and obtain their written consent to authorize ResMed to grant access to their CPAP cloud data. This approval will enable the research team to retrieve and analyze adherence data with company authorization.

Data from CPAP devices (eg, AirSense 10 AutoSet) will be collected at T1, T2, and T3, tracking the percentage of nights meeting adherence criteria. Adherence refers to the patient’s adherence to CPAP therapy, which means using CPAP for more than 70% of the total sleep time during the night, with a minimum duration of 4 hours. The calculation method involves dividing the number of days with CPAP use exceeding 4 hours by the total number of days and multiplying by 100 to obtain the average percentage of CPAP use [19].

#### Subjective Measure: Adherence to CPAP Therapy Questionnaire

We developed a self-assessed CPAP adherence and comfort levels questionnaire to allow participants to track their daily adherence and comfort levels, providing a comprehensive overview of their subjective CPAP experience.

Adherence is defined as using CPAP for at least 70% of total sleep time per night, with a minimum duration of 4 hours.Comfort levels are self-rated on a 0 to 10 scale, where 0 is extremely uncomfortable and 10 is extremely comfortable.If participants experience discomfort, they will be asked to document the specific reasons contributing to their discomfort (Multimedia Appendix 1).

This structured daily assessment enables a detailed evaluation of patient experiences, helping to identify potential barriers to CPAP use and providing valuable insights into factors influencing adherence and comfort over time.

### Secondary Outcomes

#### Common Adverse Effects Associated With CPAP

Common discomforts of using CPAP were collected and categorized based on symptoms identified by Australian scholars Ghadiri and Grunstein [6].

#### Device Usability

At the end of the study, participants will fill out a system usability scale (Multimedia Appendix 2) to evaluate system usability. This scale is a questionnaire assessing the usability of emerging technologies or systems, consisting of 10 items scored from 0 to 4 (from strongly disagree to strongly agree). The overall score is then multiplied by 2.5, with a maximum score of 100. According to Sauro [20], based on nearly 500 studies, a score of 68 is used as the benchmark for the system usability assessment: if the score is greater than 68, it indicates that the system’s usability is above 50%; if it is less than 68, the opposite is true.

#### Accuracy of Estimated Nasal Size

The AR system’s recommended nasal size compared to the case manager’s estimation shows an agreement rate approaching 95% at T0.

#### Time Required for CPAP Machine Use Education

We will calculate the time during the initial education session, hands-on training, patient questions and answers, and troubleshooting guidance at T1.

### Covariates

#### Demographic Data

We will collect participants’ gender, height, weight, waist circumference, blood pressure values, education level, presence of other comorbidities (eg, hypertension, diabetes, cardiovascular diseases, chronic obstructive pulmonary disease, asthma, cancer), smoking habits (none, once a week, once a month, once a year), drinking habits (none, once a week, once a month, once a year), exercise habits (none, once a week, once a month, once a year), history of being diagnosed with mental health disorders, napping habits, and the approximate duration of naps.

#### Clinical Indicators

The Apnea-Hypopnea Index, average blood oxygen saturation, and minimum blood oxygen saturation will be measured through polysomnography and a CPAP machine.

### Procedure

Participants diagnosed with moderate to severe OSA through polysomnography will be assessed for their willingness to participate in the study by the principal investigator. Patients who agree to undergo CPAP therapy and sign the institutional review board permit will be referred to the clinical trial. A research assistant will then contact potential participants via telephone to reconfirm their willingness to enroll. Upon confirmation, the research assistant will assist in scheduling the clinical trial and coordinating regular follow-ups at T1, T2, and T3 to assess CPAP adherence and evaluate treatment-related adverse effects (Figure 2).

**Figure 2 figure2:**
[figure not shown]
AR-guided CPAP therapy procedure followed in both the experimental group and the standard care group during the study. Data collection points were at baseline (T0), and follow-ups at 1 month (T1), 3 months (T2), and 6 months (T3) post intervention. AR: augmented reality; CPAP: continuously positive airway pressure; IRB: institutional review board; OSA: obstructive sleep apnea; Q&A: questions and answers.

### Ethical Considerations

#### Human Subject Ethics Review

This study was approved by the Institutional Review Board of National Cheng Kung University on March 1, 2023 (approval A-ER-111-531). The study adheres to all institutional guidelines and ethical principles outlined in the Declaration of Helsinki.

#### Informed Consent

All participants will provide written informed consent before enrollment. They will receive detailed explanations regarding the study objectives, procedures, and potential risks and benefits. Participants will have the right to withdraw from the study at any time without consequences.

#### Privacy and Confidentiality

All collected data will be anonymized and deidentified to protect participant privacy. Identifiable information will be securely stored and accessed only by authorized research personnel. Data will be reported in an aggregate format, ensuring that individual participants cannot be identified.

#### Compensation Details

Participants will receive financial compensation (US $6) for T2 and T3 participation. Besides that, they will be provided with comprehensive CPAP education and follow-up support as part of the study. No additional costs will be incurred by participants for their involvement.

#### No Identifiable Features of Research Participants

We confirm that no identifiable information of individual participants or users is present in any images included in the manuscript or supplementary materials.

### Data Analysis

To evaluate the effectiveness of AR-guided CPAP therapy on telemonitored adherence rates and self-reported CPAP adherence, a mixed-effects model for repeated measures will be used. This model accounts for missing data and enables comparisons of adherence rates between the two groups at T0, T1, T2, and T3. Correlation analyses will be conducted between objective CPAP adherence and the subjective adherence assessment. Data analysis was performed using SPSS version 22.0 (IBM Corp).

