**Methods:**

A randomized controlled trial with a parallel assignment will be conducted. Participants will be randomly assigned to either an experimental group receiving AR-guided CPAP therapy or a control group receiving standard care. The study will span 6 months, with assessments at baseline (T0), and with follow-ups at 1 month (T1), 3 months (T2), and 6 months (T3) post intervention. The primary outcome measure is CPAP adherence, defined as using the CPAP device for more than 70% of sleep time, with a minimum of 4 hours per night. Secondary outcomes will evaluate the common adverse effects associated with CPAP therapy, device usability, and time required for CPAP machine use education.

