## Methods

### Study Design

This parallel group randomized controlled trial is designed to evaluate the effectiveness of AR-guided CPAP therapy on patient adherence among individuals diagnosed with OSA. Participants will be randomly assigned to either the experimental group (AR-guided therapy) or the control group (standard care) by the blocking sample method. Aside from the AR component, both groups will receive identical standard care. An assistant researcher ([name]) generated the random allocation sequence, case managers enrolled participants with OSA, and an assistant researcher ([name]) assigned participants to interventions. In this study, we will blind assessors and investigators. The study will follow participants over 6 months, with data collection points at baseline (T0), and follow-ups at 1 month (T1), 3 months (T2), and 6 months (T3) post intervention.

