#### Sample Size

The sample size was determined based on a power analysis conducted for the CPAP adherence rate. Effect sizes were estimated to be 0.32 based on our previous findings, which indicated that 32.25% of CPAP-related side effects were associated with the CPAP interface [17]. A power of 0.85 was used to detect a significant difference at *P*=.05 (2-sided). Given the highly variable dropout rate for CPAP therapy, we aimed to accommodate a 20% dropout rate, which necessitated recruiting 80 participants, with 40 participants in each group.

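### Two adherence measures are listed as primary, one of them a participant-completed diary outside the blinding, and no deciding measure, time point or model term is fixed

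*Protocol article*

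**What the plan says.** The abstract is in the singular: "The primary outcome measure is CPAP adherence". It gives no time point and does not say whether the device or the participant supplies the measurement.

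The Primary Outcomes section of the Methods has two entries. The objective measure is the AirView device record, collected at T1, T2 and T3 and summarised as the percentage of days with use exceeding 4 hours. The subjective measure is a diary: "We developed a self-assessed CPAP adherence and comfort levels questionnaire to allow participants to track their daily adherence and comfort levels". Secondary Outcomes begin only after both.

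The Data Analysis section applies a mixed-effects model for repeated measures to assess "effectiveness of AR-guided CPAP therapy on telemonitored adherence rates and self-reported CPAP adherence". It says the model permits comparison of the two groups at T0, T1, T2 and T3. It also plans to correlate the objective and subjective measures.

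On sizing, "The sample size was determined based on a power analysis conducted for the CPAP adherence rate", and "A power of 0.85 was used to detect a significant difference" at a two-sided P of .05. That is the only error rate in the document.

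On blinding, the Study Design section says: "In this study, we will blind assessors and investigators". Participants are not mentioned.

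**The concern.** The abstract and the Methods disagree on how many primary outcomes there are, and the analysis text treats both adherence measures alike. With no deciding measure, visit or model term, the conclusion depends on a choice still open once results are known. More than one route to a positive result also takes the overall error rate above the stated 5%.

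The two measures are not equally reliable for a comparison between groups. One arm uses a camera-and-display AR system, while the other has its mask size checked by eye by a case manager, so participants can tell which they received. They fill in the diary themselves, so blinding assessors and investigators does not protect it. The text as it stands would let a favourable diary result count as primary evidence even if the device record showed no difference.

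**Working it through.** **The plan's own figures.** The protocol gives no overall false-positive rate, so there is none to reproduce. Its nearest figure is the sample size of 80, from an effect size of 0.32, power 0.85, two-sided 0.05 and 20% dropout. The metric of the 0.32 is not stated, so 80 cannot be verified:
- As a standardised mean difference, it gives 176 per arm: 352 in total, and 352/0.8 = 440 with dropout.
- As Cohen's f, it gives 88 in total, and 88/0.8 = 110 with dropout.
- One variant reaches 80 (64/0.8), but it needs inputs the protocol does not give: repeated measures, f = 0.32, four visits and correlation 0.6.

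That is a separate matter. What counts here is that the paragraph cites one two-sided 0.05 level for one adherence rate, without saying which measure or visit it covers.

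**Inputs for the error rate.**
- Level per test: 0.05 two-sided (Sample Size).
- Outcomes: 2 (Primary Outcomes; Data Analysis).
- Visits: 3 (T1, T2, T3). T0 is left out because participants are CPAP naive at enrolment (Inclusion Criteria), so there is no adherence to compare.
- Success rule: not stated. Assumed: any one significant test counts.
- Correlation between test statistics: not stated. Assumed common value, varied from 0.3 to 0.9.

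**Two readings of the analysis text.**
- A: one model-level test per outcome, such as the group term. k = 2.
- B: a test for each outcome at each visit. k = 2 × 3 = 6.

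**Independent tests.** The risk is 1 − (1 − 0.05)^k. For jointly normal test statistics and two-sided tests, this is also the upper bound under any correlation.
- A: 1 − 0.95² = 0.0975.
- B: 1 − 0.95⁶ = 1 − 0.7351 = 0.2649.
- For reference, the device measure alone over three visits: 1 − 0.95³ = 0.1426.

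**Correlated tests.** The risk is the probability that at least one |Z| exceeds 1.96 under a multivariate normal with common correlation ρ (simulation, 500,000 draws):

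| ρ | A: 2 tests | Device only: 3 tests | B: 6 tests |
|---|---|---|---|
| 0.3 | 9.6% | 13.6% | 24.2% |
| 0.5 | 9.0% | 12.5% | 20.7% |
| 0.7 | 8.3% | 10.9% | 16.4% |
| 0.8 | 7.8% | 9.8% | 13.8% |
| 0.9 | 7.1% | 8.3% | 10.8% |

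Letting the between-visit correlation (0.5 to 0.9) differ from the between-outcome correlation (0.3 to 0.9) gives 11.6% to 23.0% for reading B, which is much the same range.

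**After the change.** One primary test at 0.05 has a risk of 5%. Splitting the level (0.05/2 = 0.025 for two tests, 0.05/6 = 0.0083 for six) would also hold the risk to at most 5%, but would leave the diary as a route to primary success.

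**The case against.** The best defence is that the protocol leans towards one primary construct. The abstract is singular, the hypothesis concerns adherence rates, the sample size rests on the adherence rate, a calculation formula is given only for the device measure, and correlating the diary with the device suits a supporting role. These are fair pointers, but they do not settle the matter. The diary sits under Primary Outcomes, and the Data Analysis section assesses effectiveness on both measures without ranking them.

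A second defence is that multiplicity adjustment and the exact contrast are commonly left to a statistical analysis plan, which is not shown. That stands for the adjustment method, and its absence is not criticised here. It does not excuse the conflict over what is primary or the unfixed time point, which belong in the protocol.

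A reader might infer that the plan carries a false-positive risk of about 20%. The documents do not support that figure. It needs six separate tests, an any-one-counts rule and correlations near 0.5, none of which is stated. The analysis text describes what the model makes possible, not a decision rule. It does not say how daily diary entries would be summarised by visit, so comparing the diary visit by visit is itself an inference. With one test per outcome the risk is below 10%.

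A reader might also infer that the sponsor intends to claim success on the diary or at one month. Nothing in the protocol plans that; it only leaves it open. Whether the registry entry agrees cannot be judged, because the record is not at hand.

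**Conclusion.** The point holds as a conflict over the primary outcome and an unfixed primary test. The abstract has one primary outcome and the Methods have two, and no measure, time point or model term is named as decisive, against a sample size that cites a single 0.05 level. A participant-completed diary outside the stated blinding is given equal standing with the device record.

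The error rate is conditional. If any one significant test counts, it is about 7–10% (at most 9.75%) with one model-level test per outcome. It is about 11–24% (at most 26.5%) with six outcome-by-visit tests, for assumed common correlations of 0.9 to 0.3. Both ranges exceed 5%, but the protocol does not say which reading applies. These figures cover chance alone. Any reporting bias in the diary would come on top and cannot be sized from the document.

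**What to change.** Before outcome data are seen, name one primary test at two-sided 0.05 on the device-recorded percentage of nights with CPAP use exceeding 4 hours. Take it as one prespecified contrast from the planned mixed model. Two options serve: the group difference at T3 (6 months), or a single overall group effect across T1 to T3. The documents do not force the choice between them, but it must be made and written down.

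Make the diary and all other visit comparisons secondary, reported with 95% confidence intervals and no stand-alone claim of effectiveness. Align the abstract, the outcome headings and the Data Analysis text.

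Two practical points go with this. The abstract says preliminary analyses of 1-month adherence are under way, while the Results section says baseline adherence, so the sponsor should state whether any outcome data had been seen when the primary test was fixed. If T3 is chosen, the timetable needs reconciling: 40 of 80 participants are expected by September 2025 and final data collection in December 2025, yet anyone enrolled after June 2025 would not reach 6 months by then.

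The change needs no extra participants or data. Its cost is wording, and the sponsor gives up claiming success on the diary or on non-primary visits.

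### The plan does not separate stopping CPAP (known zero use) from lost data, so relying on the mixed model for missing data could bias the adherence comparison in either direction

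*Protocol article*

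**What the plan says.** The Data Analysis section applies one repeated-measures mixed model to both telemonitored and self-reported adherence, and states "This model accounts for missing data". It does not say which data it expects to be missing, or why.

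The Sample Size section states "Given the highly variable dropout rate for CPAP therapy, we aimed to accommodate a 20% dropout rate". The attrition it names is from therapy, not from data collection. With that allowance the target is 80 in total, split equally between the arms.

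The section on the objective adherence measure says "CPAP adherence will be monitored daily using AirView, a cloud-based remote monitoring system", and defines the measure by "dividing the number of days with CPAP use exceeding 4 hours by the total number of days". It does not say whether the day count runs on after a patient stops CPAP, hands the device back or leaves the study. The Informed Consent section lets participants leave whenever they wish, and it too draws no line between ending treatment and ending data collection.

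**The concern.** A likelihood-based mixed model handles missing values validly only if they are missing at random: given the visits already seen, a stopper's later values are predicted from comparable patients who carried on. For most outcomes that can be argued. Here stopping treatment is the outcome. A patient who gives up CPAP has no use on the nights that follow, and that is known. Predicting continued use for that patient replaces a known value with a wrong one.

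The Discussion expects AR to act on obstacles such as discomfort, leaks and low motivation, which are plausible reasons for giving up. If AR works partly by keeping people on CPAP, setting stoppers to missing removes that benefit from the comparison. If AR puts people off, it removes that harm.

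Early stoppers are the extreme case. Participants are CPAP-naive at entry, so there is no real adherence value at T0. Someone who quits before T1 and is set to missing contributes no adherence outcome and gives the model no earlier adherence to predict from.

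**Working it through.** **The plan's own figure.** The dropout step can be checked only in reverse: 80 × (1 − 0.20) = 64 patients, or 32 per arm, so 16 of 80 are treated as replaceable losses. The total of 80 cannot be reproduced from the stated inputs. The article says "A power of 0.85 was used to detect a significant difference" and "Effect sizes were estimated to be 0.32 based on our previous findings", but not which kind of effect size 0.32 is. Read as a standardised mean difference, it needs 176 per arm before dropout. Read as a between-group f over four visits with an assumed correlation of 0.6, it needs 64, and 64 / 0.8 = 80. The point below does not depend on which reading was meant.

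**What the allowance implies.** A stopper scored as zero use stays in the analysis and needs no replacement. Inflating the sample for dropout from therapy therefore suggests, without stating it, that these patients are expected to supply no outcome.

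**Inputs.** From the document: 40 per arm, visits at 1, 3 and 6 months, 20% dropout overall. Assumed, because the document gives none of them: mean adherence of 60 or 70 (% of nights) and stopping of 10% to 30% by arm.

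**Step 1: arithmetic.** Let m be an arm's month-6 mean if nobody stopped, and s the proportion who stop. Suppose stoppers would otherwise have resembled continuers, and that they score 0 at month 6.

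- Stoppers set to missing: the model estimates m.
- Stoppers scored 0: the mean is m(1 − s).
- Overstatement of an arm's level: m × s, never negative.
- Error in the AR minus control difference: m(AR) × s(AR) − m(control) × s(control), which can take either sign.

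| Means, control / AR | Stopping, control / AR | Means with stoppers at 0 | Difference if missing | Difference with zeros | Error |
|---|---|---|---|---|---|
| 60 / 70 | 20% / 20% | 48 / 56 | 10 | 8 | 14 − 12 = +2 |
| 60 / 70 | 25% / 15% | 45 / 59.5 | 10 | 14.5 | 10.5 − 15 = −4.5 |
| 60 / 70 | 30% / 10% | 42 / 63 | 10 | 21 | 7 − 18 = −11 |
| 60 / 60 | 25% / 15% | 45 / 51 | 0 | 6 | 9 − 15 = −6 |
| 60 / 60 | 30% / 10% | 42 / 54 | 0 | 12 | 6 − 18 = −12 |
| 60 / 70 | 10% / 30% | 54 / 49 | 10 | −5 | 21 − 6 = +15 |

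**Step 2: simulation.** This drops the assumption that stoppers resemble continuers: patients with lower underlying adherence are more likely to stop. Settings: 40 per arm, three visits, values bounded at 0 and 100, between-patient SD 18, within-patient SD 14, stoppers losing data from T2 or T3, unstructured-covariance maximum likelihood, 300 runs per scenario.

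| Means | Stopping | Mixed model, stoppers missing | Stoppers scored 0 |
|---|---|---|---|
| 60 / 70 | 20% / 20% | 8.9 | 7.0 |
| 60 / 70 | 30% / 10% | 7.9 | 18.3 |
| 60 / 60 | 30% / 10% | −1.4 | 9.9 |
| 60 / 70 | 10% / 30% | 10.2 | −3.9 |

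The pattern of Step 1 holds. With 20% stopping in each arm, the simulated levels are 60.7 and 69.7 with stoppers missing, against 49.8 and 56.9 with zeros.

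**Step 3: how far this depends on the denominator.** Scoring a stopper 0 at month 6 assumes that the T3 value covers only nights after stopping. If it covers all nights since set-up, a patient at 60% who stops at month 3 scores 60 × 3/6 = 30, and every error in Step 1 is halved. The 60 / 60 case with 30% / 10% stopping becomes 51 against 57, a difference of 6 rather than 12. The last row of the first table becomes 57 against 59.5, a difference of 2.5 rather than −5, so the sign no longer reverses. The article does not say which denominator applies.

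**The case against.** A reader might infer that the plan sets stoppers to missing, so that adherence will be overstated and a real AR effect hidden. The documents do not support that.

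- No section says stoppers are set to missing. Daily cloud monitoring with a day-count denominator, read plainly, keeps an unused night in the count as non-adherent, so a stopper would drift towards 0% while the device stays linked. This stands, and is why the point is conditional. It does not settle the matter, because the denominator after stopping, device return or withdrawal is not fixed, and the formula does not cover the self-reported measure analysed by the same model.
- The missing-data sentence may refer only to unreturned questionnaires, lost transmissions or withdrawn consent, for which a mixed model is reasonable. That is possible, but the only attrition the article quantifies is from therapy.
- A 20% allowance is routine and is not a scoring rule. Agreed: it suggests an intention and does not prove one.
- A mixed model does not simply describe those still using CPAP. It uses stoppers' earlier visits and, under missing at random, estimates the mean had they continued. That is correct, and it is the quantity used above.
- Hiding an effect is only one direction. Equal stopping exaggerates a benefit modestly, and more stopping under AR exaggerates it more.
- A condensed article leaves detail to the full protocol or analysis plan. A missing sensitivity analysis alone would be no finding. What remains is a stated claim about missing data that does not hold for the attrition the article itself plans for, if that attrition is handled as missing.

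**Conclusion.** The point holds in conditional form. The plan anticipates dropout from therapy and relies on the mixed model for missing data, without separating stopping CPAP from true data loss. If nights after stopping are set to missing, levels are overstated in both arms. The group difference is diluted when clearly more controls stop, modestly exaggerated when stopping is equal and AR continuers do better, and can show a harm as a benefit when more AR patients stop.

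All sizes rest on assumed means and stopping rates. Across the cases shown, the month-6 difference is off by between −12 and +15 points when stoppers score 0, and by half that under a cumulative denominator with stopping at month 3. If the existing formula already runs to each scheduled visit for everyone, the bias largely disappears for the telemonitored outcome and only a clarifying sentence is needed. The change should be made, because the rule can alter or reverse the estimated effect and the daily monitoring already planned largely supplies the data.

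**What to change.** State in the protocol or analysis plan that:

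1. All randomised patients are analysed in their allocated arm.
2. The telemonitored denominator is every calendar night from device set-up to the scheduled visit. If T2 and T3 values are meant to cover only the interval since the previous visit, say so and run that interval to the scheduled visit in the same way.
3. Nights without use, including all nights after stopping CPAP or returning the device, count as non-adherent.
4. Only genuinely unavailable data (lost transmission, death, withdrawn consent to data use) are missing under the mixed model, with a sensitivity analysis setting them to zero.
5. The same distinction between stopping and missing entries is stated for the self-reported measure.

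The cost is a few sentences, one reason-for-missing field in data collection, and lower reported adherence levels. Treatment and visits do not change.
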